### FIT analysis

Incoming samples will be analyzed on a daily basis, except for weekends, at three larger laboratories. One is a university clinical research laboratory; and the other two are hospital laboratories accredited according to ISO 17025 and ISO 15189, respectively. Samples will be analyzed within 5 days and kept at room temperature since the collection. The analysis will be performed using the QuikRead go® instrument (Aidian Oy) according to a Standard operating protocol (SOP) from the manufacturer. Laboratory staff will receive specific training for this purpose. A very limited number of laboratory technicians at each laboratory will be involved. Calibrations of the instrument will be carried out every week using QuikRead FOB Positive Controls.

QuikRead go® is a point-of-care FIT system that demonstrated accurate analytical performance in a recent evaluation [21]. The analytical working range of QuikRead go® is 10–200 μg Hb/g faeces (50–1000 ng/ml). Concentrations above this are displayed as > 200 μg/g, and concentrations below are displayed as < 10 μg Hb/g faeces. Accuracy will be calculated for one and two FIT and at cutoff < 10, 10–14.9, 15–19.9 and ≥ 20 μg Hb/g faeces, respectively.

The outcome of the study FIT will not be reported to participating centres. If requested for clinical purposes, physicians will have to order any FIT according to local routines.

### Reference test

The Swedish Colorectal Cancer Registry (SCRCR) is a nationwide registry for CRC with, in practice, complete coverage [22]. Benefitting from the use of personal ID numbers, study participants will be linked to this register at the latest 2 years after the date of the FIT analysis and this will serve as a reference test. In this way, we expect all patients with CRC (ICD-10 C 18–20) will be identified. Date of diagnosis of CRC will be retrieved from SCRCR, and the time period from the date of faecal sample collection until diagnosis will be calculated. Subsite (caecum, ascendens, transversum, descendens, sigmoid and rectum) and TNM stage will be requested. Patients with no CRC registered in the SCRCR within 2 years after FIT analysis will be categorized as “no CRC”. The linkage to SCRCR will also involve data on vital status (including date of death).

A new unknown proportion of patients included in the study will be referred for colonoscopy as part of the clinical workup of their symptoms. For these patients, data from colonoscopy reports will be retrieved to give an account of diagnoses with FIT concentrations below the various chosen thresholds and also to inform the health economic evaluation. Date of investigation, completeness, quality of bowel cleansing, and findings will be extracted. This will include both macroscopic and microscopic findings and be categorized as CRC, advanced adenoma, non-advanced adenoma, inflammatory bowel disease, diverticulosis/diverticulitis, angiodysplasia, and no abnormalities.

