**Method:**

A prospective, multicentre, single-gated comparative diagnostic study on quantitative FIT in patients aged 40 years and above presenting in primary care with symptoms associated with CRC will be conducted. Patients representing the whole spectrum of severity of such symptoms met with in primary care will be eligible and identified by GPs.

Participants will answer a short form on symptoms during the last month. They will provide two faecal samples from two separate days. Analyses will be performed within 5 days (QuikRead go®, Aidian Oy). The analytical working range is 10–200 μg Hb/g faeces.

Reference test will be linked to the Swedish Colorectal Cancer Registry up to 2 years after inclusion. Accuracy, area under ROC curves, and predictive values will be calculated for one FIT compared to the highest value of two FIT and at cutoff < 10, 10–14.9, 15–19.9 and ≥ 20 μg Hb/g faeces. Subgroup analyses will be conducted for patients with anaemia and those reporting rectal bleeding. A model-based cost-effectiveness analysis based on the clinical accuracy study will be performed.

Based on previous literature, we hypothesized that the sensitivity of the highest value of two FIT at cutoff 10 μg Hb/g faeces will be 95% (95% CI + / − 15%). The prevalence of CRC in the study population was estimated to be 2%, and the rate of non-responders to be 1/6. In all, 3000 patients will be invited at 30 primary care centres.

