### Design

This is a prospective, multicentre, single-gated comparative diagnostic accuracy study of a quantitative FIT in primary care, Sweden, and will be carried out according to the STARD guidelines [18]. Reference test will be linked to a cancer registry at the latest 2 years after the FIT analysis.

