### Participant identification and consent

Participants will be identified by physicians at the participating centres while listening to the history and symptoms reported by patients. Symptoms for study purposes will not be pre-specified, and it will be up to each GP to decide whether the symptoms reported by patients could be associated with CRC, to resemble the real conditions in primary care. The only restriction will be that CRC at some point during the consultation must be considered one of many possible differential diagnoses.

Physicians at participating centres will be encouraged to invite patients from the whole spectrum of severity of symptoms. There will be no specific claims related to the severity of symptoms but a bottom-line is that they must trigger a medical response of any kind. This involves possible alternatives ranging from expectancy and clinical follow-up only (e.g. discussing bowel habits again), to blood tests only (e.g. merely B-haemoglobin), routine faecal haemoglobin tests, rectoscopy only, or routine or urgent referral for complete bowel examination [20].

There will be no specific requirements on the qualifications of physicians identifying eligible patients for the study. It may involve experienced specialists in primary care as well as junior doctors, as this also resembles the real conditions in primary care.

Physicians will briefly inform and invite eligible patients to participate in the study at the consultation. Patients who are interested in participating in the study will be provided with a “study package” and a nurse assistant will demonstrate the content in detail. Patients will bring the study package back home, and if they finally decide to participate in the study, they will sign an enclosed written consent form and enclose this together with their first faecal sample. Patients will be thus identified and invited consecutively at each primary care centre, but they will not be considered included in the study until a signed written informed consent has arrived in the laboratory. First patients, to test study logistics, were included in May 2021.

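### Two years is set as the latest time for registry linkage, with no minimum, although the 'no CRC' class needs two full years of registry follow-up

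*Protocol article*

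**What the plan says.** Three places in the protocol article give the time of linkage, each as an upper limit:

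- Methods, Reference test: "study participants will be linked to this register at the latest 2 years after the date of the FIT analysis".
- Methods, Design: "Reference test will be linked to a cancer registry at the latest 2 years after the FIT analysis".
- Abstract, Method: "Reference test will be linked to the Swedish Colorectal Cancer Registry up to 2 years after inclusion".

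The Reference test section then defines the negative class: "Patients with no CRC registered in the SCRCR within 2 years after FIT analysis will be categorized as" no CRC. It also states the expected completeness: "In this way, we expect all patients with CRC (ICD-10 C 18–20) will be identified".

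Three further facts bear on the point:

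- Inclusion is spread over time. Patients are invited consecutively, and "First patients, to test study logistics, were included in May 2021" (Participant identification and consent).
- The registry is the only reference test that covers everyone. The Discussion says that colonoscopy will be available only for higher-risk patients.
- The FIT analysis section says "The outcome of the study FIT will not be reported to participating centres", and continues: "If requested for clinical purposes, physicians will have to order any FIT according to local routines".

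**The concern.** An upper limit on linkage time and a class defined by a completed 2-year window do not fit together. A patient linked at 10 or 18 months satisfies the linkage rule, but nobody can yet say that no CRC was registered within 2 years. If that patient has a cancer that is diagnosed later, the extract records no CRC, and no other reference test covers all participants to correct it.

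At stake is the reference classification behind every accuracy figure. The study is sized on sensitivity, with about 50 expected cancers and a lowest acceptable confidence limit of 80%. Few of those cancers will be FIT-negative, so losing one or two from the denominator matters. A FIT-negative cancer missed by early linkage moves from false negative to true negative, which raises both NPV and sensitivity. A FIT-positive cancer missed in the same way moves from true positive to false positive, which lowers sensitivity. The net effect on sensitivity therefore depends on which cancers are diagnosed late.

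**Working it through.** **1. The protocol's own figures (Sample size section).** The inputs are sensitivity 95%, lowest acceptable limit 80%, α = 0.05, power 80% and prevalence 2%.

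- An exact binomial test of 0.80 against 0.95 with an upper tail of 0.025 keeps power at or above 80% from n = 48 onwards. It rejects at 44 or more of 48 (tail probability 0.0248, power 0.909).
- 48 / 0.02 = 2400, hence 2352 without CRC.
- 50 / 0.02 = 2500 included, and 2500 / (1 − 1/6) = 3000 study packages.

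The stated sizes reproduce. None depends on when linkage is done.

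**2. The two rules side by side.**

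| Time of linkage after FIT | Meets the linkage rule? | Can 'no CRC within 2 years' be established? |
|---|---|---|
| 10 months | yes | no |
| 18 months | yes | no |
| exactly 24 months | yes | yes, if registration has no delay |
| after 24 months | no | yes |

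The rules agree only at exactly 24 months for each patient. A single extract that meets the upper limit for the earliest participants gives every later participant less than 2 years.

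**3. Effect on NPV.** Inputs: N = 2500 and 50 CRC (Sample size section), specificity 70% (same section), and an assumed true sensitivity of 90%, so 5 false negatives.

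- True negatives = 2450 × 0.70 = 1715.
- NPV with full follow-up = 1715 / (1715 + 5) = 99.71%.
- One false negative missed: 1716 / 1720 = 99.77%.

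The shift is 1/1720, or about 0.06 percentage points per missed case.

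**4. Effect on sensitivity if only FIT-negative cancers are missed.** The losses are assumed. Intervals are exact (Clopper-Pearson).

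| False negatives missed | Sensitivity | 95% CI | Lower limit at least 80%? |
|---|---|---|---|
| 0 of 5 | 45/50 = 90.0% | 78.2–96.7 | no |
| 1 of 5 | 45/49 = 91.8% | 80.4–97.7 | yes |
| 2 of 5 | 45/48 = 93.8% | 82.8–98.7 | yes |

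A crossing is not inevitable. From 46/50 = 92.0% (80.8–97.8), losing two false negatives gives 46/48 = 95.8% (85.7–99.5), and both lower limits exceed 80%.

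**5. Range over true sensitivity**, with 50 cancers and no FIT-positive cancer missed:

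| True sensitivity | 25% of FIT-negative cancers missed | 50% missed |
|---|---|---|
| 95% (protocol hypothesis) | 96.2% | 97.4% |
| 90% (assumed) | 92.3% | 94.7% |
| 84% (UK study cited in the Discussion) | 87.5% | 91.3% |

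**6. Effect if both kinds are missed in equal share.** If a share m of each is lost, sensitivity = TP(1 − m) / [TP(1 − m) + FN(1 − m)] = TP / (TP + FN). Sensitivity does not change. NPV still rises, because the lost false negatives become true negatives.

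**The case against.** The strongest reply is that early linkage is allowed by the wording but not planned. No section gives a linkage date, an interim extract or an end of recruitment. Read together with the explicit 2-year definition, the upper-limit phrases may simply describe the outer edge of the diagnosis window. That reading is fair, and it makes this a fault of wording rather than a chosen truncation. It does not remove the fault: the Design and Reference test sections attach the limit to the linkage itself, and an extract made early would comply with them.

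A reader might also infer that the primary sensitivity estimate will be inflated because FIT-positive patients are investigated sooner. The documents do not establish this. The study FIT result is withheld from centres, so it cannot steer work-up. Local FITs are allowed, and the Discussion notes that a test less sensitive than colonoscopy risks delaying diagnosis. These make later diagnosis of FIT-negative cancers plausible, but the article gives neither the frequency of local testing nor the timing of diagnoses.

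Three other objections stand:

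- The NPV shift is very small.
- The different clock starts (inclusion in the abstract, FIT analysis elsewhere) matter little. Inclusion occurs when the consent form sent with the first sample reaches the laboratory, and samples are analysed within 5 days.
- No registration delay is documented, so the length of any allowance is an assumption.

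Full follow-up is not free of bias either. A 2-year window may count cancers that were not present at testing, which lowers sensitivity. That is a reason to fix one window for everyone, not to let it vary with the date of inclusion.

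**Conclusion.** The inconsistency is real and stands in the current text: linkage has a maximum of 2 years and no minimum, while the negative class needs 2 complete years. Followed literally with staggered inclusion, some participants would be classed as free of CRC on less than 2 years of registry follow-up.

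The consequences are conditional on such early linkage. NPV would be slightly too high for each FIT-negative cancer missed. Sensitivity may be too high if FIT-negative cancers are diagnosed later than FIT-positive ones, and would be unbiased if both were missed in equal share. The size of any sensitivity bias rests on assumed losses, since the article gives no share of late diagnoses. The illustration shows only that, near the 80% boundary, one misclassified cancer can be enough to change the conclusion.

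This should be fixed. It does not show that truncated follow-up is intended or that the sensitivity estimate will be biased.

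**What to change.** Reword the abstract, the Design section and the Reference test section to state the same rule:

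- Link to the registry only after every participant has completed 24 months from one defined start date, for example the first faecal sample.
- Add an allowance for registration delay, with its length confirmed with the registry.
- Count only CRC with a diagnosis date within 24 months of each participant's own start date.

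Optionally, use the time from sample to diagnosis, which is already planned, to report accuracy for shorter windows as well. This would show how far the result depends on cancers that may have arisen after testing.

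The cost is a later data extract and a change of wording. Sample size and patient procedures stay as they are.

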### Sample size

Sensitivity for CRC is the most crucial aspect of FIT for potential use in symptomatic patients and we focused our study on the quest for sensitivity as high as possible. Two faecal samples for FIT may be associated with a higher sensitivity [23], and the only previous study available on QuikRead go® reported a sensitivity of 92% for one sample and 100% for the highest value of two analyses [6]. We therefore hypothesized that using maximum value/2 FIT, at cutoff ≥ 10 μg Hb/g faeces, sensitivity is 95%. We also set the lowest acceptable boundary of the 95% confidence interval at 80%. Based on *α* = 0.05, power 80% and the hypothesis of 95% sensitivity (95% CI 80–100) it was estimated that 48 patients with CRC and 2352 without CRC must be included. We also calculated the sample size according to principles provided in a recent paper [24]. In this way, it was estimated that, based on the hypothesis of sensitivity of 95% (95% CI 80–100), at least 50 patients with CRC would be needed. We reasoned false positive are far less harmful than false negatives in this context and accepted a specificity of 70% (95% CI 45–95).

The prevalence of CRC amongst patients with only low-risk symptoms in a study on FIT in primary care in Denmark was 1.5% [9]. In the present study, there will be no restrictions based on the nature or severity of symptoms, and we estimate the prevalence of CRC will be 2% in the eligible population [25]. In other words, 2500 patients, including 50 with CRC, must be included. In the previous study on QuikRead go® [6], the drop-out rate was 22% but the situation will be more advantageous for the present study as patients will receive oral information, practical instructions and all equipment needed to participate at once at their visit to the primary care centre. In all, we estimate the proportion of individuals who will accept a study package but who will not provide any faecal sample to be at most 1/6 (17%; *n* ~ 500). In summary, 3000 patients must accept receiving a study package and finally make up their minds on study participation.

### Statistical analysis

A few subanalyses are planned from the outset. Patients will be categorized according to WHO definition and Hb concentration < 120 g/L for women and < 130 g/L for men will be considered as anaemia [26]. We will estimate accuracy and predictive values for patients with anaemia vs normal haemoglobin and expect the sensitivity of FIT for CRC to be lower in patients with anaemia. We will also estimate accuracy and predictive values for patients reporting rectal bleeding vs those who do not report rectal bleeding. We expect sensitivity to be higher amongst patients reporting rectal bleeding.

### Health economic evaluation

This study is going to assess the cost-effectiveness of the different diagnostic strategies. The approach of the analysis will be a model-based cost-effectiveness analysis of the present clinical accuracy study. The following strategies will be compared.:Triage using FIT (QuikRead go® Aidian Oy), at a threshold of 10 μg Hb/g faecesTriage standard (referral straight to colonoscopy)

A diagnostic model-decision tree will be developed in order to represent the different diagnostic pathways for CRC. A measure of effectiveness will be regarded as the detection of true cases of CRC based on the results from the accuracy analysis. The cost per case detected for each diagnostic strategy and the incremental cost-effectiveness ratio will be estimated (ICER) [27]. In this case, the ICER will be the incremental cost per incremental number of true cases of CRC detected and will be calculated as follows:

$$\mathrm{ICER}\:=\:\mathrm{CtrFIT}\:-\:\mathrm{CtrSt}/\mathrm{NCtrFIT}\:-\:\mathrm{NCtrSt}$$

where CtrFIT = cost per case detected associated with triage using FIT, CtrSt = cost per case deteted associated with triage standard, NCtrFIT = number of CRC detected with triage using FIT, and NCtrSt = number of CRC detected with standard triage.

The analysis will adopt a healthcare perspective with time interval from the beginning of the screening (delivery of screening strategy) until the result of the test has been obtained. All resource use and relevant costs that will occur in this time frame will be estimated.

Data on resource use will reflect “real” life practice for the two strategies. Unit costs related to the colonoscopy will be obtained from the Cost-Per-Patient database [28]. Unit cost data of FIT, such as acquisition cost, materials/reagents costs, and maintenance costs, will be obtained from the manufacturer. Use of other healthcare resources, like consultations, various contacts with healthcare professionals (such as information/help from nurses-assistants, possible telephone contacts or on-site visits) will be estimated based on input from the accuracy study and healthcare professionals’ insights. Number and type of possible adverse events per triage strategy will be obtained from the accuracy study. Costs related to managing possible adverse events (for example with colonoscopy, bleeding, polypectomy, perforation) will be estimated based on data obtained from the Cost-Per-Patient database using the relevant procedure codes if possible (for example JFA15 for polypectomy in the colon) or otherwise through consultation with experts on the resources needed. Possible indirect costs, like administration, management, and data quality assessment will be estimated after consultation with involved health care professionals and activity times will be obtained through consultation with personnel performing each task. All labour time will be valued using the average monthly salary for each profession involved obtained from SCB Statistics Sweden.

The base case value scenario for each cost item will be estimated based on the resource utilization multiplied by unit cost and min–max values will be reported if this is possible from the input data (for example the Cost-Per-Patient database reports information on min–max values). Total cost per screening strategy, cost per case detected and ICERs will be estimated, and min–max values will be reported if possible. All costs will be reported in 2022 € euros (SEK will be converted to Euros with the exchange rate at the time of the analysis).

The robustness of the results will be explored with sensitivity analysis [29], such as one-way deterministic sensitivity analysis which investigates how the results (base case scenario) are affected by the change of the value of one parameter individually (e.g. change of the sensitivity level, use of min–max values of unit costs or resource use). Additionally, ICERs will be estimated by subgroups based on input from the accuracy analysis, such as patients reporting rectal bleeding and patients with anaemia och type of findings such as CRC stage.

The analysis will also include a budget impact analysis (BIA) associated with the implementation of triage using FIT in the primary health care setting in Sweden [30]. The total health care cost will be estimated for the different screening strategies based on the estimation of the eligible population in Sweden for screening for CRC in the primary care setting and the cost per patient for each screening strategy (base case scenario). The influence on the health care budget will be explored based on different rates of substitution of the current screening praxis with the FIT.

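### The ICER formula puts cost per case detected in its numerator, contradicting the plan's own description of the ICER as incremental cost per additional case detected

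*Protocol article*

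**What the plan says.** The Health economic evaluation section of the protocol article compares FIT triage at 10 μg Hb/g faeces with sending patients directly to colonoscopy, using a decision tree. It first describes the measure in words: "the ICER will be the incremental cost per incremental number of true cases of CRC detected and will be calculated as follows". The printed formula has a difference of two cost terms over a difference of two case terms.

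The terms are then defined. For cost: "CtrFIT = cost per case detected associated with triage using FIT, CtrSt = cost per case deteted associated with triage standard". For cases: "NCtrFIT = number of CRC detected with triage using FIT, and NCtrSt = number of CRC detected with standard triage".

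Later in the same section the planned outputs are listed: "Total cost per screening strategy, cost per case detected and ICERs will be estimated". Total cost and cost per case detected are thus separate quantities in the plan, and the formula's cost terms carry the second label. The section also plans ICERs by subgroup, including rectal bleeding and anaemia. Nothing elsewhere in the article corrects the definition.

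**The concern.** The verbal description is the standard one: extra cost divided by extra cases. The labels under the formula describe something else. Cost per case detected is already an average ratio, and subtracting two such ratios and dividing by a difference in counts divides by cases a second time.

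An analyst who codes the formula from its definitions would report a number that reads as euro per additional cancer detected but is not one. Its value would depend on how many patients are run through the tree. If subgroups were modelled at their own sizes, two with the same prevalence, accuracy and costs would get different values only because one is smaller.

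**Working it through.** The article states no numerical ICER, so there is none to reproduce. The check is algebraic, followed by an illustration.

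**Algebra.** Let T be total cost and N the cases detected, with F for FIT triage and S for the standard strategy.

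- As described in words: (T_F − T_S)/(N_F − N_S), in euro per case.
- As the terms are defined: (T_F/N_F − T_S/N_S)/(N_F − N_S), in euro per case squared.

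Multiply the modelled cohort by k. Each T and each N is multiplied by k, so each T/N is unchanged. The first ratio is unchanged and the second is divided by k. This needs no assumed costs.

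**Inputs from the Sample size section.** Prevalence: "we estimate the prevalence of CRC will be 2% in the eligible population". Cohort: "2500 patients, including 50 with CRC, must be included", which agrees with 50/0.02 = 2500. Hypothesised sensitivity is 95% for the higher of two FITs at 10 μg/g, and accepted specificity is 70%.

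**Assumptions, not in the documents.** FIT costs EUR 20, charged once per patient, and colonoscopy EUR 600. Colonoscopy has 100% sensitivity. Uptake is full in both strategies, and every FIT-positive patient has colonoscopy.

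**Calculation for 2500 patients.**

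- FIT positives: 0.95 × 50 + 0.30 × 2450 = 47.5 + 735 = 782.5
- T_F = 2500 × 20 + 782.5 × 600 = 519,500; T_S = 2500 × 600 = 1,500,000
- N_F = 47.5; N_S = 50
- Cost per case: 519,500/47.5 = 10,937 and 1,500,000/50 = 30,000
- As described: (519,500 − 1,500,000)/(47.5 − 50) = −980,500/−2.5 = 392,200
- As defined: (10,937 − 30,000)/(−2.5) = −19,063/−2.5 = 7,625

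**Same inputs per patient.** Mean costs are 519,500/2500 = 207.80 and 600. Cases per patient are 0.019 and 0.020.

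- As described: (207.80 − 600)/(−0.001) = 392,200
- As defined: (10,937 − 30,000)/(−0.001) = about 19.1 million

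| Modelled cohort | As described | As defined |
|---|---|---|
| 1 (per patient) | 392,200 | about 19.1 million |
| 500 | 392,200 | 38,126 |
| 2500 | 392,200 | 7,625 |
| 5000 | 392,200 | 3,813 |

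For 500 patients, the case difference is 9.5 − 10 = −0.5, and −19,063/−0.5 gives 38,126 before rounding of the inputs. A subgroup one fifth the size, otherwise identical, shows a figure five times larger.

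**Range over assumed unit costs**, other inputs unchanged:

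| FIT / colonoscopy (EUR) | As described | As defined, 2500 patients | As defined, per patient |
|---|---|---|---|
| 20 / 500 | 323,500 | 6,284 | 15.7 million |
| 30 / 1000 | 657,000 | 12,779 | 31.9 million |
| 50 / 1500 | 980,500 | 19,063 | 47.7 million |

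The per-patient column is the 2500-patient column multiplied by 2500.

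**Sign.** The two versions can also differ in sign, when FIT triage costs less in total but more per case detected. At an assumed and deliberately high EUR 400 for FIT against EUR 600, T_F = 1,469,500 and cost per case is 30,937 against 30,000. The defined formula gives 937/−2.5 = −375, and the described one gives −30,500/−2.5 = +12,200.

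**The case against.** The strongest reply is that this is a labelling slip. The sentence introducing the formula states the right quantity, and total cost per strategy is a planned output, so a health economist would probably compute the correct ratio. The economics is also secondary to the stated aim of accuracy and predictive values. This bears on how likely the error is to reach a result. It does not make the printed definition right, and the article separates total cost from cost per case while assigning the latter to the formula.

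Several stronger readings are tempting but are not supported.

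- *The result would depend on how many patients are recruited, and would be about 51 times too small* (392,200/7,625). The analysis is model-based, and the article does not say what cohort the tree will carry. Run per patient, the same inputs give a figure about 49 times too large (19.1 million/392,200). Dependence on the modelled cohort is established; dependence on recruitment, and a fixed size or direction of error, are not.
- *The formula lacks brackets.* This may come from typesetting or text extraction, and the point does not need it.
- *The denominator will be negative or zero, and the plan has no rule for it.* That FIT triage cannot detect more cancers than colonoscopy for all assumes equal uptake, which the article does not state. The zero case leans on the two-sample result of the earlier study, which "reported a sensitivity of 92% for one sample and 100% for the highest value of two analyses", but the economic section does not say whether one or two samples are used. The chance of no missed cancer among 50 is 0.95^50 = 7.7% at 95% sensitivity and 0.92^50 = 1.5% at 92%. A negative-over-negative ratio is valid, and its presentation is commonly left to a fuller economic plan. The abbreviation list contains terms for probabilistic sensitivity analysis and willingness to pay that the text never uses, which suggests that such a plan may exist.
- *Net monetary benefit should be required.* It needs a willingness-to-pay value per cancer detected, and the documents give none.

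**Conclusion.** The point holds as an internal contradiction in the Health economic evaluation section. The ICER is described as incremental cost per additional cancer detected but defined with cost per case in the numerator. That the literal result is in euro per case squared and varies as 1/N follows from the definitions alone. Values from subgroups modelled at different sizes would not be comparable. If every subgroup were run on one common cohort size, that particular distortion would go, but the figure would still not be a cost per additional case.

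The euro figures only illustrate and rest on the assumed unit costs, 100% colonoscopy sensitivity and full uptake. The accuracy analyses and the sample size are unaffected. The definition should be corrected before the economic analysis is programmed.

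**What to change.** Redefine CtrFIT and CtrSt as the total cost of each strategy, or as the mean cost per patient, and put NCtrFIT and NCtrSt on the same basis (total cases in that cohort, or cases per patient). Write the formula as ICER = (CtrFIT − CtrSt)/(NCtrFIT − NCtrSt). Report cost per case detected only as a separate average for each strategy. Use the same definitions for the subgroup ICERs.

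Optionally, where FIT triage costs less and detects fewer cancers, label the ratio as cost saved per CRC missed, so that a positive value is not read as the price of an extra cancer found.

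The cost is two redefined terms and one rewritten formula. No new data are needed, since total cost per strategy is already a planned output.

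### Staff time is to be valued at average salary with no employer on-costs, so built-up labour costs are understated under the stated healthcare perspective; the likely effect on strategy cost is modest

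*Protocol article*

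**What the plan says.** All the relevant text is in the Health economic evaluation section of the protocol article.

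- **Perspective and coverage:** "The analysis will adopt a healthcare perspective", and "All resource use and relevant costs that will occur in this time frame will be estimated".
- **Labour:** "All labour time will be valued using the average monthly salary for each profession involved obtained from SCB Statistics Sweden".
- **Colonoscopy:** "Unit costs related to the colonoscopy will be obtained from the Cost-Per-Patient database". The article does not say what these unit costs contain.
- **FIT:** "Unit cost data of FIT, such as acquisition cost, materials/reagents costs, and maintenance costs, will be obtained from the manufacturer". None of the examples is labour.
- **Overheads:** "Possible indirect costs, like administration, management, and data quality assessment will be estimated after consultation with involved health care professionals". Employer on-costs are not among the examples.
- **Sensitivity analysis:** one-way, changing one parameter at a time. Sensitivity, the extremes of unit costs and resource use are given as examples. Wage on-costs are not mentioned, and the only source named for extremes is the colonoscopy cost database.

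The strategies compared are FIT triage at 10 μg Hb/g and direct referral to colonoscopy.

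**The concern.** To a healthcare provider, an hour of staff time costs the salary plus whatever the employer must pay on top of it. A rule that prices all labour at salary is therefore below the provider's cost wherever on-costs exist. It does not fit the perspective and coverage that the same section adopts. This is a stated valuation basis, and applying it literally gives a low figure.

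The second issue is consistency. The article uses two costing methods: colonoscopy comes from a database, while the labour around FIT (patient instruction, contacts, probably sample handling) has to be built up from time and salary. No step is described to check that the two methods cover the same cost items. If they do not, the error falls on one side of the comparison. It would then pass into total cost, cost per case detected, the ICER and the budget impact analysis, which scales cost per patient to the eligible Swedish population.

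**Working it through.** The article states no wage, on-cost rate, labour time, unit cost or ICER, so there is no figure of its own to reproduce. What follows is an illustration with labelled assumptions.

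**Inputs from the article (Sample size section):** prevalence 2%, sensitivity 95%, specificity 70%.

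**Assumed inputs:** on-cost rate r = 20-50% of salary; FIT materials M = 0.02 of a colonoscopy's cost; FIT-specific labour valued at salary L = 0.02-0.10 of a colonoscopy's cost, with 0.20 as an extreme; colonoscopy fully costed at 1.

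**Step 1. Understatement of labour.** Share missing = 1 − 1/(1 + r).

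- r = 0.2: 1 − 1/1.2 = 16.7%
- r = 0.3: 23.1%
- r = 0.4: 28.6%
- r = 0.5: 1 − 1/1.5 = 33.3%

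**Step 2. FIT-positive share.** 0.02 × 0.95 + 0.98 × 0.30 = 0.019 + 0.294 = 0.313. So 0.687 of patients avoid colonoscopy.

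**Step 3. Strategy level, in units of one colonoscopy.** FIT strategy cost = 0.313 + L + M, rising by L × r when on-costs are added. Saving against direct colonoscopy = 0.687 − L − M, falling by the same amount.

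| L | r | FIT strategy cost | Rise | Saving | Saving overstated by |
|---|---|---|---|---|---|
| 0.02 | 0.2 | 0.353 → 0.357 | 1.1% | 0.647 → 0.643 | 0.6% |
| 0.05 | 0.5 | 0.383 → 0.408 | 6.5% | 0.617 → 0.592 | 4.2% |
| 0.10 | 0.5 | 0.433 → 0.483 | 11.5% | 0.567 → 0.517 | 9.7% |
| 0.20 | 0.2 | 0.533 → 0.573 | 7.5% | 0.467 → 0.427 | 9.4% |
| 0.20 | 0.5 | 0.533 → 0.633 | 18.8% | 0.467 → 0.367 | 27.2% |

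**Step 4. Could the sign change?** The saving vanishes when L(1 + r) = 0.687 − 0.02 = 0.667. At r = 0.5 that needs L = 0.667/1.5 = 0.445, so FIT-specific labour at salary would have to cost nearly half a colonoscopy.

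**Step 5. Dependence on specificity.** The absolute shift, L × r, does not depend on specificity, but the percentages do. The Sample size section gives 45-95% around the 70%. Take L = 0.10 and r = 0.5:

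- At 45%, the positive share is 0.019 + 0.98 × 0.55 = 0.558. Strategy cost rises 0.05/0.678 = 7.4%, and the saving goes from 0.322 to 0.272 (overstated by 18.4%).
- At 95%, the positive share is 0.019 + 0.98 × 0.05 = 0.068. Strategy cost rises 0.05/0.188 = 26.6%, and the saving goes from 0.812 to 0.762 (overstated by 6.6%).

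The sign holds in both.

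**The case against.** The strongest reply is that the article names a wage source and does not say that on-costs are excluded. It promises all relevant costs, provides separately for indirect costs, and a fuller costing plan could add a multiplier. This stands in part: one cannot conclude that on-costs will in fact be omitted. It does not remove the point, because the sentence fixes a basis for all labour time and that basis, applied as written, is too low. The indirect costs do not repair it: the items named are activities, and their staff time would be priced by the same rule.

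Other objections limit the point and stand:

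- **Direction of bias.** A reader might infer that the rule makes FIT look cheap against a fully costed colonoscopy. The article does not describe what the database contains, so that direction is conditional.
- **Reach of the rule.** It covers labour in both strategies and is not confined to the FIT pathway. Labour common to both cancels in the cost difference, and FIT-positive patients also incur the database-priced colonoscopy.
- **Hours.** A reader might also fault the plan for dividing salary by paid rather than productive hours. The article states no hours denominator, so there is nothing to fault.
- **Size.** Multiplying a 23-33% labour understatement (employer cost 1.3-1.5 times salary, assumed) by an assumed labour share of 30-70% gives about 7-23%. That describes the FIT test component. The outputs rest on strategy cost, which includes colonoscopy for the 31.3% who test positive.
- **Sensitivity analysis.** Its listed parameters are examples, so labour cost could be varied there, although on-costs are not named.
- **Weight.** The study's aim is accuracy and predictive values; no accuracy result is touched.

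**Conclusion.** The point holds as a minor one. Under a healthcare perspective, valuing all labour at average salary understates built-up staff costs, by 17-33% if on-costs are an assumed 20-50% of salary. If, and only if, the colonoscopy database holds full provider costs, labour specific to the FIT pathway is also understated relative to colonoscopy.

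At the protocol's planning values, with FIT-specific labour at 2-10% and materials at 2% of a colonoscopy's cost (assumed), the FIT strategy's cost rises by about 1-12% and the saving is overstated by about 0.6-10%. Larger percentages need labour near 20% of a colonoscopy or a specificity far from 70%. No scenario tried changes the sign of the cost difference. The documents do not support the stronger conclusion that the comparison is biased towards FIT, since the scope of the database is unknown.

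**What to change.** In the labour sentence of the Health economic evaluation section, value staff time at average salary plus employer contributions and other statutory on-costs, and state the factor used. Name that factor among the parameters varied in the one-way sensitivity analysis. Add a statement that the built-up costs and the database unit costs have been checked for the same scope, so that on-costs and overheads are neither left out on one side nor counted twice on the other.

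The cost is one multiplier, a short check of the database's documentation and slightly more costing work. The FIT cost will come out slightly less favourable. Data collection and the accuracy analysis are unaffected.
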